### Objectives and outcome measures

(1) To develop a clinical screening tool for identifying older women with back pain who are likely to have VFs. The output of this aim is a simple clinical checklist likely to consist of self-reported data and data from physical examination. The primary evaluative measure will be the accuracy of the Vfrac tool as represented by the sensitivity and specificity. The aim is for sensitivity and specificity of > 80% to justify subsequent evaluation in a definitive trial. Data from the baseline questionnaire, the physical examination and spinal radiograph will be used.

(2) To produce an online version of the combined predictors for easy use as a clinical tool (Vfrac) to identify which older women with back pain are likely to have a VF and, therefore, needs a radiograph. The output of this aim is a web-based online version of the clinical checklist (see primary objective).

(3) To model the cost-effectiveness of Vfrac based on follow-up of the participants to identify if a future definitive cluster randomised controlled trial is appropriate. The output of this aim will be an estimate of likely cost-effectiveness and a list of sources of variation that can be tested in a pilot as part of a future application for funding. Data at follow-up by self-report plus from GP electronic records will be used.

### Analysis of outcome measures—vertebral fractures

All spinal radiographs will be analysed by a trained clinician researcher for the presence of VFs using the Algorithm-Based Qualitative (ABQ) approach [32]. Images that are difficult to interpret via the ABQ method or using automated QM will be viewed by the trained clinician researcher [name] and a spinal radiologist and consensus reached. In ABQ, the diagnosis of osteoporotic fracture assumes that these fractures always involve the endplate within the vertebral ring. This method recognises that short vertebral height is not always due to fracture [33], but may be developmental or degenerative in origin. As such, the ABQ is felt to be more specific for true VF, particularly mild deformities and avoids the high false-positive rate of quantitative morphometry (QM) [34]. In addition, QM [35] will also be used to identify VFs as this method is available within automated software for the analysis of spinal radiographs and has the potential to become more commonly used within the NHS. However, QM is less specific and is associated with an increased number of false positives.

### Analysis—developing the clinical tool

Data from the questionnaires and physical examination will be linked to those from the analysis of spinal radiographs for the presence/absence of vertebral fractures. The first step will be univariable analyses to identify associations between risk factors and presence of VFs. Multiple logistic regression analyses will be performed with the aim of identifying clinical risk factors that are independently predictive of the presence of VF. All likely contenders from the univariable analysis will be included, with variables deleted in a backwards fashion whilst considering aspects such as clinical interpretation and associations between the variables, rather than relying on a simple automated basis. For example, once a final model is obtained, all deleted variables will be checked one by one to confirm if they did not contribute further. Hence, the number of variables to be considered in the multivariable modelling has not been pre-specified (on, for instance, an events per variable threshold), but the analyses will be structured, including considering variables in cognate groups, so that it is unlikely that any one model will involve more than 6–10 variables [36]. Separate analyses will then be performed to identify a cutoff to predict one or more VFs and more than one VF. Sensitivity and specificity of the pre-determined threshold will be calculated using standard techniques, comparing against the gold standard of identification of VFs from radiographs by the chief investigator using the ABQ method.

Secondary analyses will involve calculating the AUC to measure discriminative ability. To provide an estimate of the validity of the predictive models, 200 bootstrap samples of the original dataset will be derived (each bootstrap sample will be generated by randomly sampling from the original dataset with replacement 505 times). Logistic regression will then be performed on each bootstrap sample using the same set of predictor variables as in the final model, and the regression coefficients and AUC calculated. Each set of bootstrap sample coefficients will then be used to calculate AUC for the original dataset. The difference between these estimates will be used to evaluate the extent to which the discriminative ability of our final model decreases when applied to other random samples [37].

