**Fig. 2 Fig2:**
[figure not shown]
Study flowchart

The primary objective is to develop a clinical screening tool for identifying older women with back pain who are likely to have VF. The output will be a simple clinical checklist of self-reported data and data from the physical examination which will produce a binary assessment of (1) yes—this person needs a spinal radiograph, or (2) no radiograph needed. The primary evaluative measure will be the accuracy of the Vfrac tool as represented by the sensitivity and specificity of > 80%.

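### Sensitivity and specificity, the primary measure, are read against 80% on the same women used to choose predictors and cutoff, and the planned bootstrap corrects only the AUC

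*Protocol article*

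**What the plan says.** All references are to the protocol article.

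- **Aim.** Objectives and outcome measures makes accuracy the primary evaluative measure: "The aim is for sensitivity and specificity of > 80% to justify subsequent evaluation in a definitive trial". The Outline of Design and methods repeats the 80% figure and describes a single yes/no output.
- **Model building.** In Analysis—developing the clinical tool, predictors are chosen in this cohort: "All likely contenders from the univariable analysis will be included, with variables deleted in a backwards fashion". The number of candidates is not fixed in advance, though "it is unlikely that any one model will involve more than 6–10 variables".
- **Cutoff.** "Separate analyses will then be performed to identify a cutoff to predict one or more VFs and more than one VF". The next sentence reads "Sensitivity and specificity of the pre-determined threshold will be calculated using standard techniques". The article gives no threshold value and no rule for choosing one, and it describes no hold-out or external sample.
- **Validation.** This covers the AUC, under secondary analyses: "Logistic regression will then be performed on each bootstrap sample using the same set of predictor variables as in the final model". Coefficients are refitted, but predictor selection and cutoff choice are not repeated, and sensitivity and specificity are not part of the exercise.

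**The concern.** If predictors, coefficients and cutoff are all fitted to the same women, sensitivity and specificity in those women are apparent values and tend to be too high. The cutoff adds to the optimism because it can settle wherever chance has put the observed cases and non-cases in a favourable order. The plan recognises optimism, since it bootstraps the AUC, but it does not measure optimism for the quantity held against 80%. The AUC exercise would also understate it, because selection is not repeated.

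At stake is whether a tool that would fall short of 80% in new patients is reported as reaching it, and so helps to support a definitive trial.

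A smaller ambiguity is that cutoffs are sought for one or more fractures and for more than one, while the tool has one output and the analysis section does not say which target the 80% aim refers to.

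**Working it through.** **1. The plan's own figure.** Inputs from Sample size: sensitivity 85%, half-width 5%, prevalence 12%. Cases needed = 1.96² × 0.85 × 0.15 / 0.05² = 195.9. Total = 195.9 / 0.12 = 1632.7, so 1633 is reproduced. Prevalence here means any vertebral fracture, so the study is sized on one or more.

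**2. Precision at the boundary.** At 12% prevalence, 1633 women give 196 cases and 1437 non-cases. At 80% sensitivity the half-width is 1.96 × √(0.8 × 0.2 / 196) = 5.6 points.

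**3. Fixed model and cutoff, true values 78%/78%.** The exact binomial probability of observed sensitivity above 80% (157 or more of 196) is 0.270. For specificity (1150 or more of 1437) it is 0.033. Both together: 0.270 × 0.033 = 0.009, or about 1%.

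**4. Selection and cutoff tuned on the same data.** The following are assumptions, not in the article: independent normal predictors of which 8 are real, univariable screen at p<0.10, backward deletion at p<0.05, and a cutoff maximising the smaller of sensitivity and specificity. With 12% prevalence and a best attainable 78%/78%:

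| Candidates | Apparent sensitivity | Sensitivity in new patients | Gap (points) | Both apparent values >80% |
|---|---|---|---|---|
| 8 | 78.5% | 77.0% | 1.5 | 16% |
| 40 | 78.7% | 76.3% | 2.4 | 16% |
| 80 | 79.3% | 75.2% | 4.1 | 30% |

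Specificity moves little (40 candidates: 78.9% apparent, 78.6% new). Against the 1% in step 3, most of these passes come from tuning. With a best attainable 76%, only 1–4% of studies pass.

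**5. Wider range.** For equal-variance normal scores, the best equal sensitivity and specificity is Φ(Φ⁻¹(AUC)/√2), so 80%/80% needs an AUC of 0.883. Over 15–60 candidates and 12–20% prevalence, the sensitivity gap was about 1 to 3 points. Both apparent values passed 80% in:

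| True AUC | Best attainable | Studies passing |
|---|---|---|
| 0.85 | 76.8% | about 1–7% |
| 0.861–0.863 | 77.9–78.0% | about 7–28% |
| 0.875 | 79.2% | about 28–57% |

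Each setting used a few hundred simulated studies, so the percentages are approximate.

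**6. Does the remedy work?** With 60 candidates, AUC 0.861 and 12% prevalence, apparent sensitivity was 79.3% and true sensitivity 76.5%. Ten-fold cross-validation that repeated selection and cutoff choice gave 76.0%.

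**7. The two targets.** The article gives no prevalence for more than one fracture. If it were 3% (assumed; 0.03 × 1633 ≈ 49 cases), with a best attainable 78%, the gap would be about 6 points (8 candidates: 79.2% against 73.4%) to 15 points (80 candidates: 81.3% against 66.8%). The size of the bias therefore depends on which target the aim is read on.

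**The case against.** Several stronger readings are tempting, and the article does not support them.

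- **A sole go/no-go rule.** A reader might infer that passing 80% triggers the trial. The article words it as an aim "to justify subsequent evaluation in a definitive trial", and its third objective gives cost-effectiveness modelling the task of showing whether a cluster trial is appropriate.
- **Biased accuracy feeding the cost model.** This is plausible, but the cost-effectiveness section names pathway data, EQ-5D, literature and expert opinion as sources. It does not say that apparent sensitivity enters.
- **Two chances to pass.** Nothing says that the aim may be met on more than one fracture instead. The objectives, the Outline and Table 2 all point to any vertebral fracture.
- **A flat contradiction over the threshold.** 'Pre-determined' can mean determined in the sentence before. The wording is loose, but it does not show an error by itself.
- **Almost every pass is false.** In the simulated settings this is largely built in, because the AUCs were chosen below the 0.883 that 80%/80% requires.

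Three further arguments deserve weight. The bias is smaller than the 5-point planned margin. Selection is meant to involve clinical judgement, and several predictors come from earlier studies, so automated screening of many candidates may overstate the gap. At an AUC of 0.85, the one value the background reports (for pain descriptors), few studies pass falsely.

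These limit the size of the problem but do not remove it. The margin of error is symmetric, whereas optimism runs one way. Even with only the 8 real predictors as candidates, the gap was 1.5 points. An unseen analysis plan might hold the cutoff rule, but the article itself confines the bootstrap to the AUC with predictors fixed.

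**Conclusion.** The point holds in a limited form. Followed as written, the plan compares an apparent, upward-biased sensitivity with 80% and estimates optimism only for a secondary measure. For one or more fractures the bias is about 1 to 3 points in sensitivity, and close to none in specificity. It reaches about 4 points only under the largest candidate pool tried (80). It can change the conclusion for a tool truly a few points below 80%, and seldom does so at about 76% or below.

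These sizes rest on assumed candidate counts, p-value selection rules, independent normal predictors and a cutoff that balances sensitivity and specificity. The direction of the bias does not depend on those particulars. The target of the 80% aim needs stating, although the article already leans towards one or more fractures. This should be fixed; it does not invalidate the study.

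**What to change.** - **Correct the primary measure.** In each bootstrap sample (of full cohort size) or cross-validation fold, repeat predictor selection and the cutoff choice. Where selection rests on judgement, use an algorithmic stand-in and say so. Report optimism-corrected sensitivity and specificity with confidence intervals.
- **Judge the aim on corrected values.** Apply the 80% aim to these, and use them wherever tool accuracy enters the cost-effectiveness model.
- **Name the target.** State that the aim applies to one or more vertebral fractures, as Table 2 is sized, and report more than one fracture as secondary.
- **State the cutoff rule.** Replace 'pre-determined' with the rule that will be used to choose the threshold.

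The cost is a few sentences in the protocol or analysis plan, modest programming, and a reported sensitivity a few points less favourable. No extra participants or data are needed.

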We previously carried out a cross-sectional study of 509 older women from primary care, identifying four clinical triggers that could be combined in a simple tool to determine who should have spinal radiographs to identify undiagnosed osteoporotic VFs: height loss, back pain, previous fracture as an adult and rib-to-pelvis distance [13]. A cutoff from the regression equation was subsequently selected which identified all women with more than one VF and half of those with one VF. A large randomised controlled trial (RCT) of this screening tool, Cohort for skeletal health in Bristol and Avon (COSHIBA), was then undertaken in a primary care population of unselected women aged over 65 years [14]; 3200 women were recruited. Allocation to the screening arm approximately doubled the prescription of osteoporosis medications at 6 months follow-up. However, preliminary cost-effectiveness modelling suggested a cost-per-QALY of £30,000, making it unlikely that this would be cost-effective from the National Health Service (NHS) perspective in this setting, in the UK. This was mainly because of a low prevalence of VFs in this unselected population. A key finding from the National Osteoporosis Society into the realities of life with osteoporosis was that 58% of people with VFs have long-term back pain [15]. Therefore, we carried out a case-control study to look more specifically at the population of women aged over 60 years with back pain [16] to identify self-reported characteristics of pain that might help predict who has osteoporotic VFs. This study identified novel independent predictors of VF including shorter duration of back pain, pain described as crushing, pain improving on lying down and pain not spreading down the legs. Area under the curve (AUC) statistics for the combination of these factors to identify women with VFs was 0.85 (95%CI 0.79 to 0.92). Therefore, self-reported pain descriptives may identify people with back pain who have a vertebral fracture [16–18]. The Vfrac study combines the original COSHIBA screening tool with the newly identified pain descriptors (McGill questionnaire and new qualitative focus group work). Only women over 65 years with self-reported back pain will be eligible for this study. The aim of Vfrac is to produce and evaluate an improved screening tool (Vfrac) for use in older people presenting to primary care with back pain.

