A total of 1633 women aged over 65 years will be recruited via primary care from two sites within England — Bristol and Stoke-on-Trent. Potential participants will be asked for their consent via post and asked to fill in a baseline questionnaire containing items on demographics, socioeconomic status, traditional risk factors for osteoporosis, back pain, quality of life, medication use, healthcare utilisation and comorbidity. Upon the study team’s receipt of the completed baseline questionnaire and consent form, an appointment will be made for the participant to have a physical examination in secondary care followed by a lateral thoracic and lateral lumbar radiographs performed using standard NHS standard operating procedure on the same day. Before the physical examination, the participant will be asked, in person, to sign another consent form. In this consent process, they will be asked if they agree to the physical examination and radiograph. The radiograph report will be sent to the participant’s general practitioner (GP) as if the GP had ordered the radiograph. The GP practices will be given a guidance document upon recruitment, providing information on recommended pathway for patients with a vertebral fracture. This advice has been taken from the North Bristol NHS Trust guidance for GP practices within BSSG CCG (Fig. 1). The first step in this guidance is an X-ray to confirm VF.

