### Sample size

The sample size is based on the following assumptions:A prevalence of VFs between 12 and 20%, based on data from the European Vertebral Osteoporosis Study (EVOS) [12]. This is based on the general population of women under 65 years and is, therefore, likely to be lower than the true prevalence of VFs in older women with back pain.A margin of error (that is, the half-width in 95% confidence intervals of sensitivity or specificity) of 5%.Sensitivity and specificity of the Vfrac tool between 80 and 95%.

Table 2 shows the range of sample sizes according to prevalence of VFs and sensitivity or specificity of the Vfrac tool; we will aim for a sample size of 1633. This sample size will be large enough to encompass any specificity of Vfrac as sample sizes required for specificity are much lower.

**Table 2 Tab2:** Calculation showing range of sample sizes according to prevalence of vertebral fractures and sensitivity (A) or specificity (B) of the Vfrac tool

	Prevalence of vertebral fractures		
	12%	15%	20%
Sensitivity			
80%	2050	1640	1230
85%	1633	1306	980
90%	1159	927	695
95%	609	487	365
Specificity			
280	289	308	80%
232	231	245	85%
158	164	174	90%
83	86	92	95%

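### The bootstrap check of AUC draws 505 women per resample although 1633 are planned, so it does not measure the overfitting of the final model

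*Protocol article*

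**What the plan says.** The Protocol article gives the cohort size in the Abstract, under Outline ("A total of 1633 women aged over 65 years will be recruited via primary care from two sites within England") and under Sample size ("we will aim for a sample size of 1633").

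Under Analysis—developing the clinical tool, the AUC is a secondary analysis, and the validity of the model is to be judged by bootstrap: "200 bootstrap samples of the original dataset will be derived", each formed by "randomly sampling from the original dataset with replacement 505 times". In each sample the logistic model is refitted "using the same set of predictor variables as in the final model", and its coefficients and AUC are obtained. Then: "Each set of bootstrap sample coefficients will then be used to calculate AUC for the original dataset". The difference between the two AUCs is to be used to "evaluate the extent to which the discriminative ability of our final model decreases when applied to other random samples".

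The article names no dataset or subset of 505 women and gives no reason for a smaller resample.

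**The concern.** The procedure is the usual optimism bootstrap. Its logic is that a resample stands to the original dataset as the original dataset stands to the population. The drop in AUC from resample to original then mimics the drop that the final model would show in new women. This requires the resample to be as large as the dataset to which the final model was fitted. With 505 draws from 1633 women and no rescaling, the drop is that of a model built on 505 women.

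What is at stake is the estimate of how well the AUC of Vfrac would hold up elsewhere. The article describes no other check of validity for the model. The figure is also a stated instruction, not a detail left open, so an analyst following the text would carry it out.

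**Working it through.** **Inputs.** From the article: planned size 1633, 505 draws per resample, prevalence 12% to 20% (Sample size), models of about 6 to 10 variables (Analysis—developing the clinical tool), and AUC 0.85 from the earlier case-control work (Background and rationale). Assumed: a lower AUC of 0.75; independent normal predictors; 20, 50 or 80 candidate predictors, of which 6 are real; backward elimination at p<0.05 in place of the judgement-based deletion.

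**Step 1: the plan's own figure.** n = z² × Se(1−Se) / d² / prevalence = 1.96² × 0.85 × 0.15 / 0.05² / 0.12 = 1632.6, so 1633. The target is reproduced. No input in the article yields 505.

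**Step 2: what a resample holds.** 505/1633 = 30.9%. Expected fractures per resample are 505 × 0.12 = 61 to 505 × 0.20 = 101. In the full cohort they are 1633 × 0.12 = 196 to 1633 × 0.20 = 327.

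**Step 3: expected inflation.** For a fixed predictor set, optimism is roughly proportional to the number of predictors divided by the sample size. The expected factor is therefore 1633/505 = 3.23. With 1300 analysable women (an illustration) it would be 1300/505 = 2.6.

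**Step 4: simulation, predictors fixed.** There were 150 datasets of 1633 women per row, with 60 resamples each. Optimism is the AUC in the resample minus the AUC of the same coefficients in the original dataset. True optimism is the AUC in the development data minus the AUC in 15,000 new records (standard error 0.0009 to 0.0014).

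| AUC | Prevalence | Predictors | True | 1633 draws | 505 draws | Ratio | Difference |
|---|---|---|---|---|---|---|---|
| 0.75 | 12% | 6 | 0.0064 | 0.0077 | 0.0244 | 3.17 | 0.0167 |
| 0.75 | 12% | 10 | 0.0126 | 0.0135 | 0.0414 | 3.07 | 0.0279 |
| 0.75 | 20% | 6 | 0.0036 | 0.0050 | 0.0171 | 3.39 | 0.0121 |
| 0.75 | 20% | 10 | 0.0077 | 0.0096 | 0.0293 | 3.04 | 0.0196 |
| 0.85 | 12% | 6 | 0.0039 | 0.0043 | 0.0138 | 3.21 | 0.0095 |
| 0.85 | 12% | 10 | 0.0066 | 0.0078 | 0.0249 | 3.18 | 0.0171 |
| 0.85 | 20% | 6 | 0.0038 | 0.0031 | 0.0102 | 3.34 | 0.0072 |
| 0.85 | 20% | 10 | 0.0042 | 0.0056 | 0.0178 | 3.17 | 0.0122 |

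Ratio and Difference compare 505 with 1633 draws. The 1633-draw values lie within two standard errors of the truth. The 505-draw values do not.

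**Step 5: simulation, predictors first selected from the data and selection not repeated in the resamples, as the article describes.** There were 200 datasets per row, with 10 resamples each.

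| AUC | Prevalence | Candidates | True | 1633 draws | 505 draws | 505 / true |
|---|---|---|---|---|---|---|
| 0.75 | 12% | 20 | 0.0130 | 0.0071 | 0.0234 | 1.80 |
| 0.75 | 12% | 50 | 0.0256 | 0.0094 | 0.0289 | 1.13 |
| 0.75 | 12% | 80 | 0.0380 | 0.0113 | 0.0356 | 0.94 |
| 0.75 | 20% | 20 | 0.0089 | 0.0054 | 0.0177 | 1.99 |
| 0.75 | 20% | 50 | 0.0170 | 0.0068 | 0.0206 | 1.21 |
| 0.75 | 20% | 80 | 0.0269 | 0.0087 | 0.0276 | 1.03 |
| 0.85 | 12% | 20 | 0.0080 | 0.0043 | 0.0157 | 1.96 |
| 0.85 | 12% | 50 | 0.0153 | 0.0060 | 0.0185 | 1.21 |

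A shorter run (80 datasets) at AUC 0.85 and 20% prevalence gave 0.0108 from 505 draws against a true 0.0035 (standard error 0.0013) with 20 candidates, a ratio of about 3.1. With 50 candidates it gave 0.0148 against 0.0104, a ratio of 1.4. The offset therefore depends on how many predictors are screened, and with few candidates it can be negligible.

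In the table, 1633 draws without repeated selection recover 30% (0.0113/0.0380) to 61% (0.0054/0.0089) of the true optimism. With 20 candidates that estimate is closer to the truth than the 505-draw one; with 50 or 80 it is further away.

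**The case against.** **The true loss is not overstated threefold.** A reader might infer from 1633/505 that the reported loss of AUC would be three times the real one. The documents do not support that. The factor compares two versions of the same fixed-predictor bootstrap. The article chooses its predictors from the data and then holds them fixed in the resamples, which pulls optimism down. Step 5 shows the two faults partly, and sometimes wholly, cancelling. This stands. It does not justify 505, because the cancellation is accidental and turns on a candidate count that the article deliberately leaves open.

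**Correcting 505 alone may not help.** This also stands. With selection not repeated, full-size resampling can replace an estimate that is too cautious with one that is too favourable.

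**Little depends on it.** The primary evaluative measure is sensitivity and specificity, with more than 80% for both as the mark for going on to a definitive trial. Resample size touches neither, and the article ties no decision to the corrected AUC. The size is modest: at the AUC of 0.85 reported for the earlier work the difference is 0.007 to 0.017, and the article itself expects prevalence to exceed its assumed figures, which shrinks it further. This limits the weight of the point but leaves the stated number wrong.

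**The source of 505 is unknown.** The background reports "We previously carried out a cross-sectional study of 509 older women from primary care", and a reader might infer that the figure was carried over from that work. But 509 is not 505 and the article does not say so. The mismatch holds whatever its source, including a simple misprint.

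**Conclusion.** The point holds as a wrong figure in a stated rule. Followed as written, the bootstrap estimates the overfitting of a model fitted to 505 women, not of the final model fitted to the whole dataset. With fixed predictors it overstates AUC optimism by a factor of 3.0 to 3.4 relative to full-size resampling, or about 0.01 to 0.03 AUC. This assumes that close to 1633 women are analysable; the factor falls in proportion with fewer and vanishes only if the dataset itself has about 505.

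Against the true loss of discrimination the net error is usually smaller, since refitting only the selected predictors works in the other direction. The sizes rest on simulation with assumed predictor distributions, candidate counts and elimination rule. The mismatch between 505 and 1633 rests on none of these. It is a correction to a secondary analysis and does not put the primary result in doubt.

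**What to change.** Make two changes together in the bootstrap paragraph under Analysis—developing the clinical tool:

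1. Replace the 505 draws with n draws, where n is the number of women in the analysis dataset (planned 1633).
2. Repeat the variable selection in each resample. The planned deletion involves judgement and cannot be replayed exactly, so specify a rule-based approximation of it, starting from the same candidates. If this is not done, state that the reported optimism excludes selection and is therefore likely to be too small.

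The cost is two sentences of text, a little more computation over 200 resamples, and the imperfection of an approximated selection rule. Recruitment, data collection and the primary analysis are unchanged.

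### The bootstrap refits only the final predictors, so it cannot measure the optimism that comes from selecting them

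*Protocol article*

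**What the plan says.** All of this is in the protocol article, under *Analysis—developing the clinical tool*.

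- **Screening.** "The first step will be univariable analyses to identify associations between risk factors and presence of VFs".
- **Deletion.** Every likely contender then enters a multiple logistic regression, "with variables deleted in a backwards fashion whilst considering aspects such as clinical interpretation". The text says this is deliberately not a purely automated procedure.
- **Re-check.** Once a final model is reached, each deleted variable is tried again on the same data.
- **Size.** The number of variables to be considered is not fixed in advance. Variables will be looked at in related groups, and the authors expect that "it is unlikely that any one model will involve more than 6–10 variables".
- **Validation.** As a secondary analysis the AUC is calculated and 200 bootstrap samples are drawn, each of 505 draws with replacement. "Logistic regression will then be performed on each bootstrap sample using the same set of predictor variables as in the final model". The coefficients from each sample are also applied to the original data. The difference in AUC is to show how much discrimination the final model loses in other random samples.

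No passage repeats the screening or deletion inside the bootstrap, and no split-sample or external validation is described.

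**The concern.** A model chosen and fitted on the same data looks better there than it will elsewhere, for two reasons: its coefficients are tuned to those data, and its variables were picked because they did well in those data. A bootstrap that starts from the winning set treats that set as known beforehand, so it sees only the first source. The plan nevertheless gives the result the wider meaning of performance in new samples.

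The limit of 6 to 10 variables does not remove the problem. It bounds the size of one model, not the number of candidates searched. *Data collection and analysis* lists pain diagrams, PainDETECT, PHQ-9, FRAX and Q-Fracture items, McGill-type and focus-group descriptors, and six clinic measurements. Judgement used after the associations have been seen is still selection.

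At stake is the only check on the model's validity that the article describes.

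**Working it through.** **Inputs from the article.** Target size: "we will aim for a sample size of 1633". The prevalence behind that figure is 12%, the sensitivity 85% and the half-width 5 percentage points (*Sample size*, Table 2).

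**Reproducing 1633.** Women with fracture needed: 1.96² × 0.85 × 0.15 / 0.05² = 195.9. Divided by 0.12 this is 1632.7, which rounds up to 1633. So model building rests on about 196 women with fracture at 12% prevalence, or 1633 × 0.20 ≈ 327 at 20%.

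**Simulating the optimism.** The article gives no optimism figure, so the size has to be simulated.

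- *Assumptions:* N = 1633, prevalence 12%, independent standard normal candidates, six true predictors.
- *Selection rule (assumed):* univariable screen at p < 0.10, then backward deletion at p < 0.05.
- *True optimism:* AUC in the study data minus AUC of the same model in 40,000 new subjects.
- *Bootstrap optimism:* mean over resamples of (AUC in the resample − AUC of the resample's model in the original data).
- 60 datasets per setting and 40 resamples each, so the third decimal is approximate.

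| Candidates | Log odds ratio per SD | Mean variables selected | True optimism | Fixed predictors, 1633 draws | Share recovered | Fixed predictors, 505 draws | Selection repeated, 1633 draws |
|---|---|---|---|---|---|---|---|
| 20 | 0.4 | 6.4 | 0.013 | 0.008 | 59% | 0.026 | 0.018 |
| 40 | 0.4 | 7.5 | 0.021 | 0.010 | 46% | 0.030 | 0.032 |
| 80 | 0.4 | 9.5 | 0.035 | 0.012 | 34% | 0.038 | 0.055 |
| 80 | 0.2 | 8.1 | 0.075 | 0.018 | 23% | 0.052 | 0.085 |
| 120 | 0.3 | 11.5 | 0.069 | 0.017 | 25% | 0.053 | 0.084 |

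Shares use unrounded values, for example 0.0079 / 0.0133 = 59%.

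**What the table shows.**

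1. With full-size resamples, the fixed-predictor bootstrap is too small in every row. The gap grows with more candidates and weaker effects.
2. The first four rows have models of 6.4 to 9.5 variables, inside the plan's range, yet true optimism runs from 0.013 to 0.075. The search drives it more than the model size.
3. The 505-draw column is larger because each fit uses fewer women: 1633 / 505 = 3.23, and 0.0079 × 3.23 = 0.0255 against a simulated 0.0256 in the first row. That is a sample-size effect and does not measure selection. The result is above the truth in rows 1 and 2, close to it in row 3 and below it in rows 4 and 5.
4. Repeating the selection in the bootstrap overshoots in every row, by 0.005 (row 1) to 0.020 (row 3).

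**Other simulated settings with 1633 draws.**

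- 30 and 60 candidates: fixed-predictor optimism 0.010 and 0.014, against true losses of 0.019 and 0.031.
- Another set with 30 to 60 candidates and 12 to 15% prevalence: 0.006 to 0.011 against 0.018 to 0.025.
- A strong model (AUC 0.86): 0.008 against 0.010 to 0.013.
- 10-fold cross-validation with the selection repeated: 0.022 to 0.036 against a true 0.020 to 0.031, and 0.017 to 0.028 against 0.018 to 0.025. Of the methods tried, this was the closest.

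**The case against.** The strongest reply is that the harm is not established for the plan as written. A reader might infer that the validation will make the tool look more reproducible than it is. The documents do not support that: with 505 draws the estimate is inflated and exceeded the truth in several settings. In five settings with 30 to 60 candidates, four of them with correlated predictors, it gave 0.021 to 0.030 against a true 0.014 to 0.020. This objection stands. The understatement becomes definite only when the resamples are made full size.

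Three further replies carry weight.

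- The AUC is secondary. The primary measure is sensitivity and specificity, with a target above 80%, and this bootstrap does not enter it. That lowers the importance of the point.
- The gap is modest in some settings: 0.002 to 0.005 with the strong model. The only AUC in the article, 0.85, is of that order, although it comes from an earlier case-control study.
- The planned selection uses clinical judgement, and items were chosen from the literature and earlier studies, so an automated p-value search is only a stand-in. This limits confidence in the size. It does not rescue the method, because the text forces no predictor into the model and screens all of them against the outcome.

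Nor is this a detail left to a fuller plan. The article states positively which variables are refitted.

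**Conclusion.** The point holds. A bootstrap conditional on the final predictors cannot estimate the quantity that the plan assigns to it. With full-size resamples it would recover roughly a third to 60% of the true AUC optimism in most simulated settings (about 0.006 to 0.014 against 0.018 to 0.031 with 30 to 60 candidates). It would recover more in some strong-model settings, and less with more candidates or weaker effects. The mechanism, and its direction at full size, follow from the text. The size rests on assumed candidate counts, effect sizes and p-value thresholds, none of which the article gives.

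For the plan as written the direction of the net error is unknown, because the 505-draw resamples and the missing selection step pull in opposite directions. Correcting 505 alone would expose the understatement. This should be fixed; it is not critical, since the measure is secondary.

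**What to change.** 1. Write the screening, backward deletion and re-check as an explicit algorithm that stands in for the judgement-based process.
2. Repeat that algorithm inside repeated 10-fold cross-validation and report the resulting optimism in AUC. This is preferable to repeating p-value selection in a bootstrap, which over-corrects.
3. If the fixed-predictor bootstrap is kept, draw resamples as large as the analysed dataset. State that the estimate is conditional on the chosen predictors and is a lower bound on optimism.

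Uniform shrinkage of the coefficients is not part of this fix: it leaves the ranking of women, and so the AUC, unchanged.

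The cost is a few hours of programming and one paragraph, with no new data. The stand-in only approximates clinical judgement, and the reported validity may look slightly less favourable.
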